**Table 1: Primary variables (referred to as “trial progression criteria”)**

| Sufficient levels of |    | Criterion Decision                      | Green Progress | Amber Progress with changes |                           | Red Stop |
|----------------------|----|-----------------------------------------|----------------|-----------------------------|---------------------------|----------|
| Recruitment          | 1a | Rate (n of patients per site per month) | ≥0.75          | 0.46-0.74                   | Progress by adding sites. | ≤0.45    |

| Sufficient levels of |    | Criterion Decision                                                                                            | Green Progress                                                                                                                                        | Amber Progress with changes | Red Stop |
|----------------------|----|---------------------------------------------------------------------------------------------------------------|-------------------------------------------------------------------------------------------------------------------------------------------------------|-----------------------------|----------|
|                      | 1b | Number of sites open                                                                                          | ≥6 sites                                                                                                                                              | 3-5                         | ≤2       |
|                      | 1c | Total N participants recruited                                                                                | 72                                                                                                                                                    | 44-71                       | ≤43      |
| Engagement           | 2  | Proportion of phone calls answered                                                                            | ≥75%                                                                                                                                                  | 51-74%                      | ≤50%     |
| Adherence            | 3  | Proportion of intervention participants with ≥5% weight loss from baseline to the day of surgery  | ≥60%                                                                                                                                                  | 36-59%                      | ≤35%     |
| Retention            | 4  | % at final follow-up                                                                                          | ≥85%                                                                                                                                                  | 66-84%                      | ≤65%     |
| Safety               | 5  | Safety profile                                                                                                | Based on related adverse and related expected and related unexpected serious adverse events. Adjudicated by the Data Monitoring and Ethics Committee. |                             |          |

 **Adherence:** Non-adherence will be defined as <2% weight loss from baseline to the day of surgery. Participants will also rate in their weekly phone call their adherence to the intervention on a 0-100 scale.

In accordance with the multi-criteria aim, the decision to proceed would take into account

- Signal on criterion 1 (recruitment)
- Signal on criterion 5 (safety)

And if 1 and 5 are satisfactory (i.e., at least “amber”), the decision to progress will be based on the worst signal:

- If signal = RED for criteria 2 or 3 or 4 -> overall signal is RED
- Else, if no signal is RED but signal = AMBER for criteria 2 or 3 or 4 -> overall signal is AMBER
- Else, if signal = GREEN for criteria 2 and 3 and 4 -> overall signal is GREEN

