| Adherence            | 3 Proportion of intervention participants with ≥5% weight loss from baseline to the day of surgery  | ≥60%                                                                                                     | 36-59%                      | ≤35%     |
| Retention            | 4 % at final follow-up                                                                                          | ≥85%                                                                                                     | 66-84%                      | ≤65%     |
| Safety               | 5 Safety profile                                                                                                | Based on adverse and serious adverse reactions. Adjudicated by the Data Monitoring and Ethics Committee. |                             |          |

 **Adherence:** Non-adherence will be defined as <2% weight loss from baseline to the day of surgery. Participants will also rate in their weekly phone call their adherence to the intervention on a 0-100 scale.

All other outcomes will be summarised descriptively by trial arm. Where appropriate, the effect size and 95% confidence intervals will be estimated with regression models adjusting for treatment group, baseline value (where applicable), and stratification variables. Both absolute and relative effect sizes will be reported. No subgroup analyses are planned.

Complications will be summarised using:

- count/percentage of participants with any complication
- count/percentage of participants with any complication by grade
- count/percentage of participants with the highest grade of complication reported
- count/percentage of participants with any type of complication
- count of total complications.

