**Table 3: a simple list of all primary variables and their measurement**

| Type                  | Objectives               | Outcome Measures                                                                                                     | Definition                                             |
|-----------------------|--------------------------|----------------------------------------------------------------------------------------------------------------------|--------------------------------------------------------|
| Primary (Recruitment) | 1a. Recruitment variable | Recruitment Rate                                                                                                     | n of patients recruited per site per month             |
| Primary (Recruitment) | 1b. Recruitment variable | Number of sites open                                                                                                 | Integer (0-n)                                          |
| Primary (Recruitment) | 1c. Recruitment variable | Total number of participants recruited                                                                               | Integer (0-n)                                          |
| Primary (Safety)      | 5. Safety profile        | Based on related adverse events and expected related and unexpected related serious adverse events                   | Type, number of and percentage of each event category. |
| Primary (Engagement)  | 2. Engagement variable   | Proportion of phone calls answered. This is defined as the “mean percentage of phone calls answered per participant” | Percentage (0-100%)                                    |
| Primary (Adherence)   | 3. Adherence variable    | Proportion of intervention participants with ≥5% weight loss from baseline to the day of surgery                     | Percentage (0-100%)                                    |
| Primary (Retention)   | 4. Retention variable    | % at final follow-up                                                                                                 | Percentage (0-100%)                                    |

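### SAP 3.7.1 uses safety and recruitment only as an at-least-AMBER gate, so an AMBER verdict on either still returns an overall GREEN, and safety has no defined colours

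*Combined protocol and SAP*

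**What the plan says.** The protocol's primary objective is to judge whether a definitive trial is justified, and safety profile is one of its five listed primary outcome measures (Synopsis). Protocol Table 2 (section 11.2) and SAP Table 1 (section 3.7.1) give numeric GREEN, AMBER and RED bands for recruitment, engagement, adherence and retention. The column headings give the colours their meaning: progress, progress with changes, stop.

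Safety has no bands. Protocol Table 2 says "Based on adverse and serious adverse reactions. Adjudicated by the Data Monitoring and Ethics Committee"; SAP Table 1 says "Based on related adverse and related expected and related unexpected serious adverse events. Adjudicated by the Data Monitoring and Ethics Committee". SAP Table 3 defines the measure as "Type, number of and percentage of each event category".

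Only the SAP says how the criteria combine. The decision takes account of the signals on criteria 1 and 5, and then: "And if 1 and 5 are satisfactory (i.e., at least “amber”), the decision to progress will be based on the worst signal". Three lines set the overall signal from there. A RED on engagement, adherence or retention makes it RED; failing that, an AMBER on any of those three makes it AMBER. The last line reads "Else, if signal = GREEN for criteria 2 and 3 and 4 -> overall signal is GREEN". None of the three lines names recruitment or safety.

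SAP 3.7.1 also says that the confidence intervals are descriptive and play no part in the decision to progress, so the colours carry it.

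**The concern.** The rule announces a worst-signal principle but applies it to three of the five criteria. The gate separates RED from not-RED and treats AMBER and GREEN alike. If the committee judges that changes are needed on safety grounds, the algorithm has no place to record that, and its output is the one that Table 1 reserves for progressing without changes. Recruitment is handled the same way: the AMBER cell for criterion 1a names a change to make (adding sites), yet AMBER recruitment with criteria 2 to 4 GREEN also returns GREEN.

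Two further gaps sit beside this. Nothing follows the gate for the case where criterion 1 or 5 fails it. And the gate tests safety against a colour that no table defines and no text asks the committee to give.

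At stake is the headline answer to the primary objective. An overall signal that cannot show a safety reservation is a weak summary for a trial of a diet of about 800 kcal/day before cancer surgery, where protocol 9.6.1 expects one person in five to have an adverse event, mostly mild, due to the intervention.

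**Working it through.** **The plan's own figure.** SAP 3.3 states a collective power of 85%, from 93% × 92% × 99% = 84.7%. With a one-sided 5% test, power = Φ{[p1 − p0 − 1.645·√(p0(1−p0)/n)] / √(p1(1−p1)/n)}:

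- Engagement, 0.50 against 0.75, n = 36: Φ[(0.25 − 0.137)/0.0722] = 94.1%
- Adherence, 0.35 against 0.60, n = 36: Φ[(0.25 − 0.131)/0.0816] = 92.8%
- Retention, 0.65 against 0.85, n = 72: Φ[(0.20 − 0.092)/0.0421] = 99.5%

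The product is 86.9%, within two points of the stated 85%. The figure concerns criteria 2 to 4 only. Safety and recruitment do not enter it, so it neither supports nor weakens this point.

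**The decision rule.** Inputs: the gate and the three lines of SAP 3.7.1, taken literally. Criterion 1 is treated as one signal (an assumption, since the SAP gives no rule for combining 1a, 1b and 1c), and safety is assumed to receive a colour. Five criteria with three colours each give 3^5 = 243 combinations.

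- Passing the gate: 2 × 2 colour pairs for criteria 1 and 5, times 3^3 = 27 patterns of criteria 2 to 4, gives 108.
- Within each set of 27: one is all GREEN; 2^3 − 1 = 7 have no RED but at least one AMBER; 27 − 8 = 19 have at least one RED.
- Overall signals as written: 4 × 1 = 4 GREEN, 4 × 7 = 28 AMBER, 4 × 19 = 76 RED.
- Failing the gate, with no stated signal: 243 − 108 = 135. Of these, 81 have RED safety, which is every combination with RED safety.

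With criteria 2, 3 and 4 all GREEN:

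| Recruitment | Safety | Overall as written | Worst of criteria 1 to 5 |
|---|---|---|---|
| GREEN | GREEN | GREEN | GREEN |
| GREEN | AMBER | GREEN | AMBER |
| AMBER | GREEN | GREEN | AMBER |
| AMBER | AMBER | GREEN | AMBER |
| GREEN or AMBER | RED | none stated | RED |
| RED | any | none stated | RED |

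Two of the four GREEN outcomes carry AMBER safety; three of the four carry AMBER on at least one gate criterion. Under a worst-of-five rule the totals become 1 GREEN, 28 + 3 = 31 AMBER and 76 + 135 = 211 RED.

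**The case against.** A gate on recruitment and safety followed by a worst-of-three rule is a recognisable design, and it matches SAP 3.3, whose collective power covers engagement, adherence and retention only. Leaving safety to independent adjudication, with the Trial Steering Committee acting as the monitoring committee (protocol 13.3, SAP 3.4.3), is legitimate; event-count thresholds in a trial of 72 would not obviously be better. The condition of at least AMBER may itself imply that the committee returns a colour. The committee's charter and the Data Definitions and Tables document, which the SAP calls integral, are not available here and may say more.

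Much of this stands, and it rules out some stronger readings:

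- A reader might infer that a RED safety verdict has no consequence. The documents do not support that: the RED column is headed Stop, and RED fails a written precondition for progressing. Only the explicit overall signal is missing.
- A reader might infer that safety is ignored, or that a bare GREEN would be published. Safety is taken into account as a gate and reported in its own right, and nothing says the overall signal will appear without the safety verdict.
- A reader might infer that delegating the verdict is itself an error. It is not.

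What the objection does not answer is the AMBER case. Discretion over the verdict is no reason for the rule to drop the verdict once given. A charter that defined the colours would not repair this, because the loss occurs in the SAP's three lines.

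**Conclusion.** The point holds as a conflict between the SAP's combination rule and its own column headings and worst-signal principle. AMBER on safety, on recruitment or on both, with criteria 2 to 4 GREEN, returns an overall GREEN: three of the four routes to GREEN, two of them with AMBER safety. For RED on criterion 1 or 5 the defect is smaller: the outcome can be inferred but is not written as a signal.

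The counts describe the rule and say nothing about how often an AMBER verdict will arise; the documents give no basis for that. The conclusion assumes that the three lines are applied as written, that criterion 1 yields one colour, and that the committee returns a colour for safety. The finding that no safety colour is requested or defined is limited to the protocol, the SAP and its supplementary document on secondary outcomes.

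**What to change.** In SAP 3.7.1, with a matching entry in protocol Table 2:

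1. Keep adjudication with the committee, but require one of three verdicts for criterion 5: GREEN (progress), AMBER (progress with changes, which it names) or RED (stop). No event threshold is proposed here.
2. Have the committee document and date the basis for its verdict before the final analysis and before any further review of data by arm. A basis set before any by-arm data were seen may no longer be possible: SAP version 2.0 is dated 7 October 2024, close to the planned end of recruitment in November 2024, and SAP 3.6 provides for by-group reports in closed sessions.
3. Take the worst signal over criteria 1 to 5, so that RED on 1 or 5 gives overall RED and AMBER on 1 or 5 caps the overall signal at AMBER.
4. State how 1a, 1b and 1c combine into one recruitment signal, since step 3 needs it.

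The cost is SAP, protocol and charter wording, with no new data. Protocol 11.1 already provides for SAP review and a documented amendment before database lock. The sample size and the stated 85% for criteria 2 to 4 do not change. The downside is that an overall GREEN becomes slightly harder to reach. How much harder depends on step 4: criterion 1c is GREEN only at 72, so if the worst of 1a to 1c is used, a total of 71 would cap the overall signal at AMBER.

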### 3.7.2 Secondary and other outcomes

All other outcomes will be summarised descriptively by trial group. Where appropriate, the effect size and 95% confidence intervals will be estimated with regression models adjusting for treatment group, baseline value (where applicable), and stratification variables. Further details regarding the secondary outcomes will be provided at a later date, (provisionally in a supplementary document) prior to database lock. Both absolute and relative effect sizes will be reported.

Complications will be summarised using:

- count/percentage of participants with any complication
- count/percentage of participants with any complication by grade
- count/percentage of participants with the highest grade of complication reported
- count/percentage of participants with any type of complication
- count of total complications.

## 4. STATISTICAL PRINCIPLES

### 4.1 Statistical Significance and Multiple Testing

*See also the protocol section “The Level of Statistical Significance”*

P-values will not be reported given the feasibility nature of the trial. There will be no adjustment for multiple testing. The 95% confidence intervals will be presented but regarded as nominal and descriptive.

### 4.2 Definition of Analysis Populations

*See also the protocol section “Analysis populations”*

All randomised and eligible participants that underwent surgery will be included in the main analysis on an intention-to-treat principle regardless of withdrawal or non-adherence. A per protocol analysis will include the subsample of intervention participants who achieved  $\geq 5\%$  weight loss from baseline to the day of surgery. The adverse event analysis will include the participants in the control group and the participants commencing the intervention in the intervention group. Participants who had their surgery less than 20 days since randomisation will be included in this analysis.

## 5. TRIAL POPULATION AND DESCRIPTIVE ANALYSES

This is a summary of flow of trial participants through the trial and baseline stratification, demographic and clinical characteristics of each group.

### 5.1 Representativeness of Study Sample and Patient Throughput

*See also the protocol appendix “Study Flow Chart” and the appendices in this SAP.*

The flow of participants through each stage of the trial, including numbers of participants randomly assigned, receiving intended treatment, completing the study protocol, and analysed for the primary outcome is provided following the appropriate guideline (e.g. CONSORT flow diagram). Protocol violations/deviations and information relating to the screening data including the number of ineligible patients randomised, together with reasons, information on number of participants screened, found to be ineligible (with reasons where available), refused to participate (with reasons where available) will be included as applicable.

The trial flowchart is given in the Appendices.

### 5.2 Withdrawal from treatment and/or follow-up

*See also the protocol section “Informed Consent” and section “Early Discontinuation/Withdrawal of Participants”*

Once enrolled and during the course of the study a participant may choose to withdraw early from the intervention at any time for any reason. This may happen for several reasons, including but not limited to:

- The occurrence of what the participant perceives as an intolerable AE.
- Inability to comply with study procedures
- Participant decision

The numbers (and percentages) of withdrawals will be reported by treatment group along with the reasons for these withdrawals. These will be summarised as per the table below.

**Table 2. Details Of Withdrawals (And Reasons) Split By Treatment Group**

| Treatment    | Patient ID | Date of withdrawal (DDMonYYYY) | Reasons for withdrawal |
|--------------|------------|--------------------------------|------------------------|
| Intervention | ID 1       |                                |                        |
|              | ID 2       |                                |                        |
|              | ...        |                                |                        |
| Control      | ID 1       |                                |                        |
|              | ID 2       |                                |                        |
|              | ...        |                                |                        |

### 5.3 Baseline Characteristics

*See also the protocol sections “Baseline Assessments” and the relevant tables in the SAP DDT*

The baseline face-to-face assessment will be conducted during the screening visit at each site. Baseline characteristics are reported by treatment group, including the stratification/minimisation factors and any other variable deemed relevant.

Numbers (with percentages) for binary and categorical variables and mean (and standard deviation), or median (with lower and upper quartiles) for continuous variables will be presented; there will be no tests of statistical significance nor confidence intervals for differences between randomised groups on any baseline variable.

### 5.4 Unblinding

*See also the protocol section “Blinding and code-breaking”*

The nature of the study precludes blinding of participants and research nurses. Unblinding of the central research team and independent assessors of the post-operative complications (as per 3.2 and 3.6) may occur only following recommendations of the TSDMEC.

### 5.5 Treatment Adherence with Details of Intervention

*See also the protocol sections “Protocol Deviations”, “Study Monitoring” and “Serious Breaches”*

The number of people in each arm receiving their randomised treatment will be reported. The adherence of the randomised participant to the intervention and control pre-surgery will be checked and reported as per the protocol. Adherence with the protocol and the SOPs and any post-surgery complications will be checked and reported as per the protocol.

### 5.6 Reliability

The REDCap database will incorporate range and logic checks. Manual checks may be carried on the data to ensure plausibility on the recognisance of the Trial Statistician.

## 6. ANALYSIS

### 6.1 Outcome Definitions

*See also the protocol section “Synopsis”*

The primary variables for this trial are referred to as “trial progression criteria” and a list of those primary outcomes is given below. The study also has secondary outcomes (morbidity, oncological outcomes, etc) which are not listed separately here as a comprehensive list can be found in the “synopsis” section of the protocol.

**Table 3: a simple list of all primary variables and their measurement**

| Type                  | Objectives               | Outcome Measures                                                                                                     | Definition                                             |
|-----------------------|--------------------------|----------------------------------------------------------------------------------------------------------------------|--------------------------------------------------------|
| Primary (Recruitment) | 1a. Recruitment variable | Recruitment Rate                                                                                                     | n of patients recruited per site per month             |
| Primary (Recruitment) | 1b. Recruitment variable | Number of sites open                                                                                                 | Integer (0-n)                                          |
| Primary (Recruitment) | 1c. Recruitment variable | Total number of participants recruited                                                                               | Integer (0-n)                                          |
| Primary (Safety)      | 5. Safety profile        | Based on related adverse events and expected related and unexpected related serious adverse events                   | Type, number of and percentage of each event category. |
| Primary (Engagement)  | 2. Engagement variable   | Proportion of phone calls answered. This is defined as the “mean percentage of phone calls answered per participant” | Percentage (0-100%)                                    |
| Primary (Adherence)   | 3. Adherence variable    | Proportion of intervention participants with ≥5% weight loss from baseline to the day of surgery                     | Percentage (0-100%)                                    |
| Primary (Retention)   | 4. Retention variable    | % at final follow-up                                                                                                 | Percentage (0-100%)                                    |

